**1. Study Purpose and Rationale**

**Primary Aims**

This randomized controlled trial was designed to test the efficacy of Project WORTH (Women on the Road to Health), a four session group-based multimedia HIV/STI prevention intervention for drug-involved female offenders recruited from community supervision settings in New York City. For this trial, 306 women were randomized to either: (1) a four-session traditional group-based HIV/STI intervention (traditional WORTH); (2) a four-session multimedia group-based HIV/STI intervention (multimedia WORTH); or (3) a four-session group-based Wellness Promotion intervention that served as an attentional control condition.

This study examined two primary hypotheses: (1) ‘‘intervention effect’’ -- whether the WORTH HIV/STI risk-reduction intervention delivered by either the traditional or multimedia method would be more efficacious in addressing the following primary outcomes: decreasing the number of self-reported unprotected sex acts, increasing the proportion of protected sex, and increasing consistent condom use, as well as secondary outcomes of reducing the incidence of biologically confirmed STIs over the 12-month follow-up period when compared to the Wellness Promotion control condition; and (2) ‘‘modality effect’’-- whether the multimedia HIV/STI risk-reduction intervention would be more efficacious in decreasing the number of unprotected sex acts, increasing the proportion of protected sex, and reducing incidence of biologically confirmed STIs when compared to the traditional method.

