**Randomization and masking**

We randomly assigned groups of four to nine women to receive one of the three conditions. The computer-generated randomization algorithm was designed to balance the number of women per study arm via an adaptive, biased-coin procedure. The investigator who designed the randomization program was not involved in conducting the trial, but was involved in the statistical analysis. Investigators were masked to treatment assignment until the final 12-month follow-up assessment was completed in April 2013. Data were locked in September 2013 and the study arms were unmasked.

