When a participant arrives for their pre-intervention assessment, they undergo a shortened version of the screener to confirm eligibility. If a woman no longer meets eligibility criteria, she is compensated $10 and will no longer participate in the study. Women who meet eligibility criteria undergo a pre-intervention assessment. The pre-intervention assessment is conducted in a private room and lasts approximately 60 minutes, consisting of demographic information, drug and alcohol use, sexual behaviors, intimate partner violence, measures of depression and PTSD, to be completed on ACASI. Biological assessment for STIs at the baseline assessment involves providing pre-test counseling, asking female participants to provide a vaginal swab (self administered by the participant) which is used to test for gonorrhea, Chlamydia and trichomoniasis, and then providing follow up post-test counseling to notify participants of their results and treatment referrals as needed. Additionally, at baseline assessment, all participants are asked to provide an oral swab to conduct testing for HIV infection, using the OraQuick ADVANCE 15-min oral fluid assay ("rapid test"). We have been approved for Hazardous Materials and currently have a Data Use Agreement with Emory University in Atlanta, GA. (please see attachment) to process the samples collected. Emory University has conducted a number of STI testing protocols for research studies.

**Pre- and Post-test Counseling for HIV/STI Testing:** All participants receive pre-and post-test counseling for HIV and STI testing as mandated by New York State law. Prior to being asked to provide an oral specimen, using the OraQuick test procedures to confirm their HIV serostatus, all participants will receive standard HIV pre-test counseling from the Clinical Research Coordinator (CRC) who be trained and supervised in the conduct of such counseling. Because all study participants receive pre- and post-HIV/STI test counseling, all participants (regardless of condition) are exposed to HIV risk reduction information including sex risk reduction, which helps participants avoid becoming infected with HIV or STIs. Thus, participants in all conditions receive higher quality pre/post HIV/STI test counseling than is the general standard of care outside the study protocol. These procedures are being used in our current studies and are in compliance with the most up-to-date New York State and New York City laws and standards.

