**Biospecimen Collection, Shipping and Testing Procedures for STIs:** To complement self-reports and provide a more objective outcome, we use biological assays for gonorrhea, Chlamydia, and trichomonas. These STIs are selected based on their high prevalence and incidence in this population, the availability of accurate tests, and because each can be definitively treated with a single oral dose of antimicrobial medication. We assess STIs with DNA amplification assays on self-collected vaginal swab specimens from the women, which have several advantages including stability for transport and ease of collection. Each participant will be asked to obtain one vaginal specimen by inserting a sterile Dacron-tipped swab about 2.5 inches or as far as comfortable into the vagina, rotating it for 15 to 30 seconds, and removing it. The vaginal swabs are placed into separate specimen transport packaging. Refrigerators are utilized for storing specimens between shipment dates. Specimens are shipped within 72 hours of collection. All specimens are shipped and processed by Emory University in Atlanta, GA, using standard handling procedures in specially designed biohazard containers suitable for Dangerous Goods Shipping according to International Air Transport Association (IATA) guidelines. Emory University has worked on other NIH funded studies involving STI testing.

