The basic format of each WORTH session remains consistent following a sequence of 5 steps: (1) an opening (grounding meditation) which provides a brief centering transition to engage participants in the work of the sessions (2) Check-in to review material from the previous session, and to discuss any incidents where participants engaged in risk behaviors and to acknowledge positive ways in which women used new skills to avoid HIV risk; (3) a discussion using case vignettes to raise awareness of links between IPV, drug-related activities, and HIV risks; (4) a skills-building component relevant to the discussion; and (5) review and update participant needs, goal development for skills-building at home, and a closing ritual. The WORTH intervention consists of four 2-hour group sessions that are led by two female facilitators. The main objectives of each session are detailed below:

Session 1: HIV information, risk, and rationalizations: (1) introduce purpose and goals of group; (2) elicit group rules, roles and obtain a commitment of confidentiality; (3) elicit reasons for wanting to take care of one’s self; (4) provide basic information about HIV disease, transmission and treatment; (5) provide basic information about STI symptoms, transmission and treatment; (6) weigh the pros and cons of HIV testing and learn how to seek testing and counseling; (7) discuss behaviors that increase health and longevity for those living with HIV; (8) make HIV and STIs more real and personal in our lives; (9) increase awareness of attitudes that put us at risk of getting HIV or STIs; (10) strengthen participants ability to challenge risk rationalizations; (11) introduction to social support network map (12) setting HIV risk reduction, social support and help-seeking goals (13) closing, homework, and WORTH affirmation.

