• Recording mechanism captures all content and activities from the session, including interactive content for each participant, such as participant’s goals, motivations, individualized social network maps and agreed upon ground rules, as well as any other important information the participants or facilitator want to document. The computer tracks any data that the facilitator or participants enter during the sessions. This mechanism yields more precise quality assurance data on the amount of time spent on each activity and the level of participant engagement in different activities.

• Facilitator interactive guide which acts as a road map, prompting the facilitator to move sequentially through each activity without the need to rely on notes, memory or previous experience. The separate interface for facilitators uses the same computer support tool but contains a road map that guides the facilitator through the session activities and contains additional information, concepts, and models just for facilitators.

**Condition 3- Wellness Promotion:** The Wellness Promotion condition consists of general health information that is not gender-specific. SIG has used versions of this Wellness Promotion condition in previous studies such as Eban and Connect. Session content will be as follows:

Session 1: Diseases that affect women; reasons to keep ourselves healthy; prevention, detection and treatment; health risk assessment; goal setting. Session 2: Exercise assessment; benefits of exercise; physical activity for fitness; introduction to nutrition; body mass index; healthy personal eating; goal setting. Session 3: smoking and your health; alcohol; cancers and screening; getting health care; communicating with health care providers. Session 4: Attitudes about exercise; early detection and screening review; improving communication with health care providers; health basketball; graduation.

Participants are compensated $30 for each intervention session completed. Upon completion of condition 1, 2, or 3, participants complete follow-up assessments at 3-, 6-, and 12-months post-intervention. The 12-month follow-up assessment includes biological specimen testing for HIV and STI’s. All follow-up assessments are completed at the Social Intervention Group Community Research Center, and participants are compensated as follows: 3-month assessment: $35, 6­month: $50, and 12­month: $65.

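### STI outcome is called 12-month incidence, but swabs at baseline and month 12 alone measure STI positivity at month 12

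*Protocol*

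**What the plan says.** **The claim.** Section 1, Primary Aims, gives as part of the first hypothesis "secondary outcomes of reducing the incidence of biologically confirmed STIs over the 12-month follow-up period", comparing WORTH by either method with Wellness Promotion. The second hypothesis repeats it for multimedia WORTH: "reducing incidence of biologically confirmed STIs when compared to the traditional method".

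**The specimens.** Section 3, Study Procedures, places the first swab before the intervention: "Biological assessment for STIs at the baseline assessment involves providing pre-test counseling". The second comes at the end: "The 12-month follow-up assessment includes biological specimen testing for HIV", a sentence that goes on to name STIs. The payments agree: HIV/STI tests are mentioned with the baseline and 12-month payments, while the 3- and 6-month visits are described as assessments only.

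**The infections.** The three STIs were chosen partly because "each can be definitively treated with a single oral dose of antimicrobial medication". Women positive at baseline are referred for treatment, and staff confirm that it was received.

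**Content bearing on care-seeking.** WORTH Session 1 aims to "provide basic information about STI symptoms, transmission and treatment". Wellness Promotion covers detection, screening, getting health care and talking with providers. Secondary Aim 2 lists service utilization among the mediators.

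**The concern.** Incidence over a period counts every new infection in that period. Two swabs about a year apart, for infections that can be cured, show only who is infected on the second day. A woman infected in month 4 and treated in month 5 counts as uninfected.

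Two things are at stake. First, the label: a month-12 prevalence reported as 12-month incidence understates acquisition and claims something that was not observed. Second, the comparison: month-12 positivity depends on how fast infections are treated as well as on how often they are acquired. An intervention that changes care-seeking can therefore move this outcome without changing acquisition. STI status is the only biological outcome in either hypothesis, so a reader will give it weight as the objective check on self-reported behaviour.

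**Working it through.** **1. Schedule against claim.** Every place that gives a swab time point says baseline or month 12. No sentence rules out swabs at 3 or 6 months, so that they are absent is an inference, but a consistent one. The protocol describes no procedure for confirming or counting infections diagnosed and treated between the swabs.

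**2. Model.** The protocol states no STI rate, clearance rate or power, so there is no figure to reproduce. For illustration, let L be the infection rate and g the treatment-or-clearance rate, both per year, in women uninfected at the start and swabbed one year later. (The real interval is somewhat longer, because follow-up is timed from the end of the intervention.)

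- Cumulative incidence = 1 − exp(−L)
- Month-12 positivity = L/(L+g) × [1 − exp(−(L+g))]

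Assumed ranges: L 0.15 to 0.40, g 0.5 to 2.0.

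**3. Share of infected women seen.** With L = 0.25 and g = 1.0, cumulative incidence is 1 − exp(−0.25) = 22.1%. Positivity is 0.25/1.25 × [1 − exp(−1.25)] = 0.200 × 0.7135 = 14.3%. The share seen is 14.3/22.1 = 65%. Over the assumed ranges it runs from 44% (L = 0.15, g = 2.0) to 80% (L = 0.40, g = 0.5).

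**4. Equal clearance in both arms.** Take L = 0.14 against 0.20. Cumulative incidence is 13.1% against 18.1%, ratio 0.72.

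| g, both arms | Positivity, L = 0.14 | Positivity, L = 0.20 | Ratio |
|---|---|---|---|
| 1 | 8.4% | 11.7% | 0.72 |
| 2 | 5.8% | 8.1% | 0.71 |
| 4 | 3.3% | 4.7% | 0.71 |

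The ratio survives even at g = 4, beyond the assumed range. What is lost is events.

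**5. Faster clearance in WORTH, equal infection.** Take L = 0.25 in both arms and control g = 1.0, so control positivity is 14.3%.

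| WORTH clearance relative to control | WORTH positivity | Apparent odds ratio |
|---|---|---|
| 1.25 times | 12.9% | 0.89 |
| 1.5 times | 11.8% | 0.80 |
| 2 times | 9.9% | 0.66 |

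Over the assumed ranges the apparent odds ratio runs from 0.94 to 0.55 with no difference in infections. The protocol says that "306 women were randomized to either" one of three arms and that allocation was "designed to balance the number of women per study arm via an adaptive, biased-coin procedure". That suggests about 306/3 = 102 per arm, or 204 WORTH against 102 control. At those sizes a two-sided 5% test would favour WORTH with probability 21% in the 2-times case (about 4% to 38% over the ranges), against a nominal 2.5%. This treats women as independent and ignores dropout.

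**6. Faster clearance in control.** Suppose WORTH truly lowers the infection rate by 30% (L = 0.175 against 0.25), with WORTH g = 1.0. The true cumulative-incidence ratio is 16.1/22.1 = 0.73. WORTH positivity is 10.3%. Control positivity is 11.8% if its clearance is 1.5 per year (ratio 0.87) and 9.9% if 2.0 (ratio 1.04). A real benefit is shrunk or hidden.

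**7. Carry-over of untreated baseline infection.** If 5% of women start infected, positivity rises by 0.05 × exp(−1.25) = 1.4 points, from 14.3% to 15.7%.

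**The case against.** The strongest reply is that undercounting alone does not distort the comparison. Step 4 bears this out: with equal clearance the positivity ratio tracks the incidence ratio. The share of infections missed is a loss of events and precision, and cannot be presented as a false treatment effect.

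A reader might infer from WORTH's teaching on STI symptoms and treatment that the schedule favours WORTH. The documents do not support that. Wellness Promotion also deals with detection, screening and getting care, and all arms receive test counselling, results and treatment referral. Bias needs clearance to differ between arms. Naming service utilization as a mediator makes that plausible, but nothing fixes its direction. Between multimedia and traditional WORTH the argument is weak, because both deliver the same core elements.

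A reader might also infer that month-12 positivity has little to do with new infection. That goes too far. Baseline infections are referred and their treatment confirmed, so most month-12 positives should be new and step 7 is a small effect. The measure is an undercount of incidence.

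Finally, an analysis plan that is not shown may define the variable, adjust for baseline and say how baseline-positive women are counted. Silence on those rules is no fault in the protocol. What stands is that no analysis plan can recover confirmed infections that were never sampled.

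**Conclusion.** The stated outcome and the specimen schedule do not match. The design supports a statement about STI positivity at month 12 and does not support one about incidence over 12 months. This follows from the protocol's own text and needs no assumed rate, beyond reading the described swab times as complete.

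The sizes do rest on assumption. Under the rates used here the late swab sees 44% to 80% of ever-infected women. The effect on the comparison runs from almost none (equal clearance) to a spurious odds ratio as low as 0.55, or a masked benefit, if clearance differs by up to a factor of two. A claim that the trial is biased towards WORTH would go beyond the evidence; the direction is open.

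The point concerns the three curable STIs. HIV persists, so baseline and month-12 tests can show new HIV infection. The first hypothesis ranks STI as secondary, and the behavioural primary outcomes are untouched. Severity: should-fix.

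**What to change.** In both hypotheses under Primary Aims, restate the STI outcome as positive for gonorrhea, Chlamydia or trichomonas at the 12-month visit. Adjust the comparison for the baseline STI result, which is already collected. Do not describe the result as a reduction in 12-month incidence.

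If the service-use data include STI testing or treatment during follow-up, report them by arm beside the swab result, so that a reader can judge whether clearance is likely to have differed. New swabs or questionnaire items are not an option: the section on randomization and masking says that the last 12-month follow-up was completed in April 2013 and data were locked in September 2013.

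The cost is a change of wording, one covariate and, where the data exist, one descriptive table. The downside is a less ambitious claim.

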**Secondary Aims**

Aim 1: To test whether key variables moderate the treatment effects of the intervention. Moderators for the proposed study will include socio-demographics, childhood sexual abuse history, substance abuse history, criminal justice history, type of offense, IPV history, number and type of sexual partners in the past year, and baseline STI and HIV Status.

Aim 2: To test whether there is evidence that our theoretical mediator variables do indeed mediate the treatment effects of the intervention on outcomes. Mediators will include HIV/STI knowledge, condom use outcome expectancies and intentions, condom use self-efficacy, coping and self-regulation skills, IPV self-efficacy, sexual negotiation skills, condom negotiation self-efficacy, peer norms for HIV risk reduction, social support and service utilization.

Aim 3: To determine the level of fidelity with which the Multimedia Worth and Traditional Worth are implemented (e.g.., adherence to protocol, attendance, and facilitator competency in delivering the intervention) that may interact with primary STI and condom use outcomes.

**Rationale for the study:**

HIV/AIDS and criminal justice involvement are critical public health issues for women. Women consistently represent the highest risk group for HIV infection, and the Centers for Disease Control (2004) report an HIV positive rate of 9.2 per 100,000 among U.S. women. The proportion of AIDS cases in women increased by 123% between 1991 and 1997, more than any other group. Women are also the fastest growing segment of the criminal justice population in all 50 states, with U.S. female imprisonment growing 757% since 1977. Between 1990 and 1996 the number of convicted female defendants grew at 2 1/2 times the rate of increase for males. Although overall HIV rates in prisons have been decreasing since 1999, incarcerated women continue to display significantly higher rates of HIV than incarcerated males. An alarming 18.1% of female jail inmates in New York City tested positive for HIV in 1998. Additionally, female drug users are at high risk for heterosexual transmission of HIV, both from sexual relationships with male drug users as well as having sex under the influence of drugs, which may lead to hypersexuality, disinhibition, and the possibility of exchanging sex for money or drugs.

While it is clear that women inmates in jails and prisons bear a high burden of HIV/AIDS, the effective development of prevention interventions for this high-risk group require an understanding of HIV risk context, sexual behaviors and attitudes for women while they are still in the community and before they become heavily involved in the criminal justice system. HIV prevention interventions must focus on women at early points of entry into the criminal justice system, when they are still in the community and at higher risk of engaging in unsafe sex and drug behaviors. This study focuses on a population of drug-involved women who have been arrested and given a court sanction, but are still living in the community. The parent study (WORTH) has demonstrated effectiveness with drug-involved women in a variety of settings.

**2. Study Design and Statistical Procedures**

The proposed design is a randomized controlled trial, consisting of three conditions for a total of 306 intervention participants. For this study we recruited and screen women from community-based criminal justice settings (e.g. community courts and probation sites) who meet eligibility criteria. Eligible participants complete a pre-intervention assessment, after which they will be randomized into one of three conditions. Condition 1 will be a four-session, multimedia, gender specific, group HIV prevention intervention (Multimedia WORTH); condition 2 will be the traditional pencil and paper implementation of WORTH (Traditional WORTH); and condition 3 will be a 4-session Wellness promotion condition (Wellness Promotion). After completing each condition, participants complete 3-month, 6-month and 12-month follow-up assessments. Participants are compensated for participating in screening, pre-assessments, and all follow up assessments, and given travel reimbursement for attending intervention sessions

**Randomization and masking**

We randomly assigned groups of four to nine women to receive one of the three conditions. The computer-generated randomization algorithm was designed to balance the number of women per study arm via an adaptive, biased-coin procedure. The investigator who designed the randomization program was not involved in conducting the trial, but was involved in the statistical analysis. Investigators were masked to treatment assignment until the final 12-month follow-up assessment was completed in April 2013. Data were locked in September 2013 and the study arms were unmasked.

